## Intervention

### Intervention group

Patients in the intervention group will attend a follow-up clinic two monthly for up to 6 months after discharge from the hospital. Screening instruments will be utilised on the first visit and appropriate management and referral provided. These will involve: overall medical review involving all systems assessment, medications, vital signs, physical activity assessment, muscle strength,^30^ assessment of mobility (*modified Rivermead Mobility Index*),^31^ balance assessment (*Berg Balance measure*),^32^ discussion with carer as to concerns (*Zarit Burden Interview*),^33^ screening for chronic pain syndromes (*Brief Pain Inventory*),^34^ nutritional review, screening with the (*PTSD*) *Checklist-Civilian Version* (for post-traumatic stress syndrome),^35^
*generalised anxiety disorder (GAD-7*)^36^ and *The Patient Health Questionnaire-9 for depression.*^37^ Following the results of the screening and team discussion, participants and/or carer will be referred to appropriate agencies including the general practitioner, specialist, physiotherapist, nutritionist, speech pathologist, exercise physiologist, psychologist and/or occupational therapist. These instruments are screens for post-ICU problems that have been identified in previous studies.^13–20^ Members of the research team include an intensivist/thoracic physician, two specialist respiratory physiotherapists, a psychologist, a senior nurse researcher, a professor of community and general practice and a health economist/community physiotherapist. This individualised management is in line with recommendations of the NICE clinical guidelines.^8^

### Standard care

Patients in the control group will have usual care, that is, they will be referred to specialist outpatient clinics and/or general practitioners on discharge.

### Subgroup—rural patients

A small number of patients (10) originally managed in the major quaternary level ICU will be discharged to a rural area. We will test the feasibility of providing follow-up care to these patients. These patients will also be randomised to either the intervention or the usual care group. The patients will be interviewed via telemedicine (videoconferencing)^26^ and a research assistant will be appointed to complete other screening tools and refer them to appropriate agencies. If specialist services are required, for example, chronic pain clinic, these may also be accessed via telemedicine.

## Outcome measures

### Primary measure

The primary measure will be HRQoL as measured by the Short Form 36 health survey V.2 (SF36V.2)^38^ which demonstrates content and construct validity, sensitivity and responsiveness to change in many patient groups^39^ including ICU and postsepsis survivors.^40^ Pilot testing of the SF36 in this population by this team has been conducted in a current trial of inpatients postsepsis and has shown excellent completion rates at 6 months by telephone.^41^

### Secondary measures

Patients’ readmission rates to hospital (medical record data), 12-month mortality (only expectedtrend) and economics and healthcare resource use. The latter will be monitored through examination of patient medical records, patient self-report and through Medicare/Pharmaceutical Benefits Scheme data extraction. The SF6D^42^ is a preference based six-dimensional health state measure suitable for economic evaluation that is derived from the SF36. The SF6D defines 249 health states, and a summary utility score for the SF6D will be calculated using UK weights.

Individual patient productivity will be measured using a work/activity impairment questionnaire, the Work Productivity and Activity Impairment Questionnaire (WPAI).^43^

The outcome measure of SF36V.2 will be taken at baseline, 6 and 12 months postenrolment in the study. All other measures (mortality, hospital readmission and economic and health resource use) will be taken at 6 and 12 months postenrolment.

### Sample size

Power calculations are based on SF36 using previously published Minimally Clinically Important Differences (MCIDs) for the SF36 physical domain scores of 7.8 points (SD 15) in our pilot trial on rehabilitation in sepsis.^41^ The sample size, based on a two sample comparison of means was calculated at 78/group for the SF36 at 90% power with a two-sided, α error level of 0.05. Allowing for an almost 30% loss to follow-up (mortality, dropouts), a total of 204 participants will be required.^44^

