## Background

Greater numbers of patients are surviving in intensive care units (ICUs) but a new syndrome called the ‘post-ICU syndrome’ has appeared with residual physical, cognitive and psychosocial problems lasting from 5 to 15 years.^1^
^2^ The rate of a major illness recurring and/or mortality is also increased in the year after ICU discharge, with mortality ranging from 26% to 63% at 1-year postdischarge in long-stay ICU patients (≥48 h).^3^ ICU survivors additionally often have a number of problems^1–4^ including debility and fatigue from loss of muscle mass, ongoing nutritional problems, difficulty in dealing with altered appearance and function, chronic pain,^5^ amnesia and delusional symptoms. All of these factors have a major impact on the health and productivity of survivors and their carers, survivors’ return to work rates, as well as the impact on availability of ICU and hospital beds, surgical waiting lists, health costs and society.^6^ There has been a ‘call to arms’ to provide improved management regimes to ICU survivors.^7^ The National Institute of Health and Care Excellence (NICE) clinical guidelines^8^ provided by the National Health Service (NHS) NICE recommend ‘optimisation of recovery’ rather than merely survival post-ICU. All of these problems are particularly present in survivors of sepsis.^9^

Sepsis is defined as a powerful inflammatory response to severe infection.^10^ The annual total cost of sepsis syndromes in the USA is $16.7 billion nationally^11^ with the incidence projected to increase by 1.5% per annum as patients develop more comorbidities and resistant organisms. In brief, sepsis is a major public health concern.^12^

However, the statistics above do not include the cost of ongoing disability and loss of productivity postillness. Patients with sepsis syndromes have significantly worse outcomes with lower health-related quality of life (HRQoL),^13–16^ particularly in the physical domain,^17^
^18^ chronic pain^5^
^19^ and cognitive domain^20^ compared with non-septic ICU survivors. While other critically ill/injured or disabled patients, for example, those with burns, strokes, head injuries have established follow-up regimes, patients with sepsis are not referred to formal rehabilitation and are discharged home with extremely poor function.

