#### Inclusion criteria

Patients included will be men or women ≥18 years of age, with a documented episode(s) of sepsis^10^ (≥2 criteria of a systemic inflammatory response plus proven or strongly suspected infection, severe sepsis defined as sepsis plus organ failure, septic shock defined as severe sepsis not responding to management) and required respiratory support for longer than 48 h. Enrolment in the study should be within 1 month of discharge from hospital.

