### Randomisation

Participants will be randomised by opaque sealed envelopes after enrolment. Numbers on the envelopes will be generated by a computer-generated randomisation (http://www.randomization.com) table based on blocks of four to assign patients to either the intervention or the usual care group. The randomisation sequence will be concealed from consent designee staff and protected by an electronic password. Participants will be stratified based on a score >3 on the Cumulative Illness Rating Scale (CIRS-G).^29^

We are stratifying patients as most patients who develop sepsis syndromes have a number of comorbidities, but there can be a small number of relatively young, healthy patients who are affected. The allocation sequence will be generated by the research assistant attached to the trial. Patients will be consented by the chief investigator ([name]) and assigned to interventions by a second investigator (PT).

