### Methods for protecting against other sources of bias

This study will be double blinded with the assessors, data analysts and a number of investigators (TC, FC and GM) blinded from group allocation. There will be concealed allocation of participants. Participants will be stratified for CIRS-G.^29^ Participants when being consented will be told that they will be in one of the two groups which will be followed up posthospital and they may need to attend an outpatient clinic. Patients are unaware of the usual follow-up posthospital so should not feel they are receiving an increased/decreased level of care. Both groups will be contacted by telephone for completion of HRQoL life instruments at the required stages. Participants may have varying severity of illness, lengths of stay and/or time on mechanical ventilation in ICU; however, this will be compared between groups and if unequal adjusted models using the relevant covariates will be presented as well as unadjusted comparisons.

A few participants in either group may be referred to rehabilitation by their treating physician. This will be compared between groups. A number of patients may be uncontactable for final outcome measures; however, we have had a 95% rate in the current trial at 6 months postsepsis.^41^ The GEE^46^ will allow for missing data. If patients ‘cross-over’, that is, do not receive the planned intervention, they will still be analysed with the group they originally enrolled as per intention to treat.

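### With 204 randomised and the stated loss of almost 30%, power at 12 months is about 87%, not 90%, and that loss allowance fits only the lowest one-year mortality the protocol cites

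*Protocol article*

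**What the plan says.** The Sample size section takes its difference and standard deviation from "SF36 physical domain scores of 7.8 points (SD 15) in our pilot trial on rehabilitation in sepsis" and reports a sample size "calculated at 78/group for the SF36 at 90% power with a two-sided, α error level of 0.05". It then makes a single allowance for deaths and dropouts combined: "Allowing for an almost 30% loss to follow-up (mortality, dropouts), a total of 204 participants will be required".

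Four other places in the protocol article bear on that allowance:

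- The Background cites one-year outcomes "with mortality ranging from 26% to 63% at 1-year postdischarge in long-stay ICU patients (≥48 h"). It is the only mortality figure in the article.
- The Inclusion criteria admit patients who "required respiratory support for longer than 48 h", so the trial population resembles that group.
- The section on protecting against other sources of bias reports the team's own follow-up success: "we have had a 95% rate in the current trial at 6 months postsepsis".
- The Secondary measures section sets the SF36 at baseline, 6 months and 12 months. No time point is named as primary, and the planned analysis is a GEE across time points.

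**The concern.** Two things do not fit. First, 204 is too small to leave 78 per group after a loss of almost 30%, so the stated power, size and loss cannot all be true together.

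Second, the SF36 can be collected only from living patients, and the allowance has to absorb death as well as dropout. Against the mortality range in the Background, almost 30% leaves room for the lowest value and nothing above it. The article does not say why the lowest value should apply.

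At stake is how a null result would be read. A reader told that the trial had 90% power would treat a non-significant 12-month difference as firmer evidence against a 7.8-point benefit than the number of observed patients supports.

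**Working it through.** **Inputs.** Difference 7.8, SD 15, two-sided 0.05, 90% power, 78 per group, loss of almost 30% and total 204 are all from Sample size. Equal allocation (102 per group) is inferred from the per-group figure and from randomisation "based on blocks of four to assign patients to either the intervention or the usual care group". One-year mortality of 26% to 63% is from the Background. Non-contact among survivors is taken as 5%, from the 95% rate at 6 months; that it holds at 12 months is an assumption.

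**Step 1: reproduce 78 per group.** n = 2 x [(1.960 + 1.282) x 15/7.8]² = 77.7, rounded up to 78. At 78 per group, power is 90.1% by the normal approximation and 89.7% by the t distribution. The printed figure is sound.

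**Step 2: reproduce 204.**

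- 78 x 1.30 = 101.4, rounded up to 102 per group, total 204. This matches.
- Dividing by the retained fraction gives 156/0.70 = 222.9, so 223 (224 if rounded within group). This does not match.
- Reading almost 30% as 28% or 29% gives 156/0.72 = 217 or 156/0.71 = 220. Neither matches.

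The article does not print its formula, so multiplication by 1.30 is an inference. What follows does not depend on it: 1 − 156/204 = 23.5% is the largest loss that leaves 156 evaluable.

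**Step 3: power at the stated loss.** 102 x 0.70 = 71.4 per group. Power for a two-sample comparison is 87.4% (normal) or 87.0% (t). With loss at 28% it is 88.3% (normal).

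**Step 4: compare the allowance with the cited mortality.** Total loss = 1 − (1 − mortality) x 0.95. Evaluable per group = 102 x (1 − mortality) x 0.95. Power is from the two-sample t-test with d = 7.8/15 = 0.52.

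| 12-month mortality | Total loss | Evaluable per group | Power at 12 months |
|---|---|---|---|
| 26% (lowest cited) | 29.7% | 71.7 | 87.1% |
| 35% | 38.3% | 63.0 | 82.5% |
| 44.5% (midpoint) | 47.3% | 53.8 | 76.2% |

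With no dropout at all, 26% mortality leaves 102 x 0.74 = 75.5 per group, still short of 78, with power of about 89%.

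**Step 5: separate the two causes.** With 102 per group and 5% non-contact, 78 evaluable requires mortality of at most 1 − (78/102)/0.95 = 19.5%. With 223 randomised (111.5 per group) the limit is 1 − (78/111.5)/0.95 = 26.4%. Most of the gap between 19.5% and the cited range therefore comes from the inflation step. Correcting that step would restore 90% only at about the lowest cited mortality.

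**The case against.** The strongest objection concerns the mortality range. A reader might infer that the 90% claim fails over the whole of 26% to 63%, with power down to about 58% at the top. The documents do not support that as a finding. The range is background for long-stay ICU patients in general and is not this trial's planning assumption. Patients are randomised shortly before leaving hospital, so ward deaths after ICU are already excluded, and palliative and haematological patients are not eligible. Both features may put mortality below the range. The sentence "All of these problems are particularly present in survivors of sepsis" closes a paragraph mostly about function, pain, nutrition and cost, and gives no sepsis mortality. This objection stands: values above 26% are scenarios.

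A reader might also infer that the trial needs 12-month mortality under about 19% to keep its power, as a fault of the mortality assumption. Step 5 shows that this threshold is largely a product of the inflation step.

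Nor is the power claim unconditional: the loss allowance follows it directly. The trouble is that the condition, taken at its word, does not deliver the power.

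The 12-month two-sample comparison is also only one reading of the primary analysis. The GEE uses 6-month data too, when fewer patients will have died, and an effect pooled over visits may have more power. How much cannot be computed from the article. However, the protocol sized the trial on a two-sample comparison of means, and no model recovers 12-month scores from patients who have died.

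Finally, a full protocol may justify the loss rate where a condensed article does not. That could answer the question of where almost 30% comes from. It would not reconcile 78 per group, almost 30% and 204, which stand together on the page.

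**Conclusion.** The point holds in two parts of different strength.

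The firm part needs no mortality assumption. The stated size and stated loss do not give the stated power: 204 tolerates 23.5% loss, and at 30% loss the power of the protocol's own two-sample comparison is about 87%. The shortfall is about 3 percentage points, or some 19 patients (223 against 204).

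The conditional part is that the combined allowance fits only the lowest one-year mortality the protocol cites. If mortality were higher within that range, 12-month power would be lower, for example 82.5% at 35% and 76% at 44.5%. This rests on 1:1 allocation, 5% non-contact persisting to 12 months, a single-time-point comparison, and the relevance of a general long-stay ICU range to this cohort. The article does not settle the last of these, so it does not show that the trial will be badly underpowered.

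**What to change.** In the Sample size section, replace the 90% claim with the power that 204 gives at the stated loss: about 87% at 30% loss, and 90% only if total loss is no more than about 23.5%. State expected 12-month mortality and non-contact separately, each with its source; if the team's pilot sepsis trial supplies a mortality figure for patients alive at hospital discharge, use that one. Give 12-month power over a plausible range of loss, and say that these figures refer to a two-sample comparison at 12 months, since the GEE may do better.

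This is a rewrite of one paragraph. It adds no patients and changes no procedure. Its cost is a less favourable stated power.

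### The total of 204 covers 23.5% loss to follow-up, not almost 30%; at 28–30% loss the stated calculation gives about 87–88% power instead of 90%

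*Protocol article*

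**What the plan says.** All the inputs are in the Sample size section of the protocol article. The effect and spread are given as "SF36 physical domain scores of 7.8 points (SD 15) in our pilot trial on rehabilitation in sepsis". The evaluable number, for a two-sample comparison of means, "was calculated at 78/group for the SF36 at 90% power with a two-sided, α error level of 0.05". The allowance for loss follows directly: "Allowing for an almost 30% loss to follow-up (mortality, dropouts), a total of 204 participants will be required".

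The Abstract repeats the total of 204. No other power, loss rate or derivation is attached to that number anywhere in the article. Equal allocation is not stated as a ratio, but it is implied by the equal group sizes and the blocks of four described under Randomisation.

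**The concern.** Loss to follow-up is a fraction of those randomised, so the evaluable number has to be divided by the fraction retained. Multiplying it by one plus the loss rate gives too small a total, and the gap widens as the loss rate rises. The step from 156 to 204 looks like such a multiplication.

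What is at stake is how the trial's size is described. The section invites the reader to believe that 90% power survives a loss of almost 30%, deaths included. If it does not, a null result would be read against a slightly higher power than the calculation supports.

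**Working it through.** **Inputs (Sample size section).** Difference δ = 7.8; SD σ = 15; two-sided α = 0.05 (z = 1.960); power 90% (z = 1.282); 78 evaluable per group; total 204, so 102 per group. The loss rate is given only as almost 30%, so I take 28%, 29% and 30% as the range.

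**Step 1: reproduce the evaluable number.**
n per group = 2 × [(1.960 + 1.282) × 15 / 7.8]² = 77.7, rounded up to 78. The stated figure reproduces. Power at 78 per group is 90.1% by the normal approximation and 89.7% by the noncentral t.

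**Step 2: the loss that 204 can absorb.**
Spare participants: 204 − 156 = 48.
As a share of those randomised: 48/204 = 23.5%.
As a share of those evaluable: 48/156 = 30.8%.
Only the first is a loss-to-follow-up rate.

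**Step 3: the total required at the stated loss.** N = n / (1 − loss). The two columns differ only in where rounding up is done.

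| Loss | From the total of 156 | From 78 per group |
|---|---|---|
| 28% | 156/0.72 → 217 | 109 per group, 218 |
| 29% | 156/0.71 → 220 | 110 per group, 220 |
| 30% | 156/0.70 → 223 | 112 per group, 224 |

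None of these is 204. Multiplication does reach it: 78 × 1.3 = 101.4, rounded up to 102 per group, gives 204 exactly.

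**Step 4: power with 204 at the stated loss.** Retained per group = 102 × (1 − loss). Normal-approximation power = Φ(δ / (σ√(2/n)) − 1.960). For 30% loss, n = 71.4, and (7.8/15) × √(71.4/2) = 3.107; subtracting 1.960 leaves 1.147, and Φ(1.147) = 87.4%.

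| Loss | Retained per group | Power (normal) | Power (t) |
|---|---|---|---|
| 23.5% | 78.0 | 90.1% | 89.7% |
| 28% | 73.4 | 88.3% | 87.9% |
| 29% | 72.4 | 87.9% | 87.5% |
| 30% | 71.4 | 87.4% | 87.0% |

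**Step 5: one internal comparison.** The Background section cites one-year deaths, "with mortality ranging from 26% to 63% at 1-year postdischarge in long-stay ICU patients (≥48 h". Taking only the lowest value, 26%, with no other loss: 102 × 0.74 = 75.5 per group, and power is about 89%. That single figure exceeds the true 23.5% allowance but costs only about one point of power.

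**The case against.** **The shortfall is small.** This stands. Power falls by about 2 to 3 points, equivalent to roughly 13 to 20 participants (217 − 204 to 224 − 204). At 28% loss the normal-approximation power, 88.3%, is within 2 points of 90%. No conclusion of the trial is likely to turn on it. That limits the severity, but it does not make the sentence correct.

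**The planned analysis is more efficient than the calculation.** The Planned statistical analysis section specifies generalised estimating equations over repeated measurements, which use partial follow-up and may recover some power. For illustration, if baseline were adjusted for and correlated about 0.29 with the outcome (an assumption; the article gives neither), the required number would be 78 × (1 − 0.29²) = 71.4 per group, which restores 90%. So it would be too strong to say that the trial lacks 90% power under its planned analysis. What can be said is that the stated calculation does not show it, because that calculation rests on a two-sample comparison of means with loss allowed for separately.

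**The team reports 95% contact.** The section on other sources of bias cites this rate at 6 months in another trial. It suggests that dropout may be low, but the stated allowance also includes mortality, and the contact rate does not make 204 consistent with almost 30%.

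**The cause is inferred.** This also stands. The article does not show how 204 was reached. Multiplication by 1.3 fits exactly, but it remains an explanation and not a documented step.

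**A stronger reading to resist.** A reader might apply the upper part of the 26–63% mortality range to the randomised groups and infer that the 12-month comparison is badly underpowered. The documents do not support this. The range describes long-stay intensive care patients in general, in the year after ICU discharge. Trial participants are randomised later, just before leaving hospital, and those needing palliative care are excluded. Carrying the 6-month contact rate forward to 12 months would be a further unsupported step. Whether the assumed loss is realistic is a separate question from the arithmetic.

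**Conclusion.** Wrong as written, and should be corrected; the consequence is modest. The 78 per group is sound. The 204 supports 90% power up to 23.5% loss, and at 28–30% loss the article's own method gives about 87–88%. Nothing else in the article reconciles 204 with almost 30%.

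This rests on equal allocation, equal loss in the two groups, the stated difference and SD, and reading almost 30% as 28–30%. It concerns the stated two-sample calculation and makes no claim about the power of the estimating-equation analysis. The lowest cited mortality shows that the true margin is narrower than it appears, and the documents support no more than that.

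**What to change.** Replace the sentence on loss with wording such as: *204 participants give 90% power with up to 23.5% loss to follow-up; with 30% loss (about 71 per group) power is about 87%.*

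This costs one sentence and a slightly less favourable power statement. Enrolment, design and analysis stay as they are. If the sponsor preferred to keep 90% power at 30% loss, the matching total would be 223, or 224 in blocks of four, but restating the figure is sufficient.
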